### Aims and hypotheses

#### Aims

The purpose of the proposed school-based research is to evaluate the efficacy and net economic benefits of a novel teledental pathway of dental care in improving the oral health outcomes of school children.

#### Objectives

To determine the efficacy of a novel teledental pathway of dental care in improving oral health outcomes of school children relative to the usual pathway of dental care. *Hypothesis: The teledental pathway of dental care would be as effective as a routine pathway of dental care in improving children’s oral health.*To compare the costs of the teledental and usual pathway of dental care in school children, from a health system perspective. *Hypothesis: The teledental pathway of dental care would be cost-saving relative to the usual pathway of dental care.*To assess the diagnostic performance of dental screening on the basis of dental images relative to the reference visual dental inspection at the baseline. *Hypothesis: The photographic dental assessment will be as accurate and reliable as the standard visual dental screening.*

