The proposed project builds on previous validation trials that examined the feasibility of the teledentistry approach to dental screening [25–27]. The findings showed that the use of dental photography in dental screening is feasible and offered a moderate diagnostic accuracy relative to visual dental screening. Recent systematic reviews indicated that most reviewed studies concerned with teledental diagnosis demonstrated comparable results between photographic and visual inspection techniques [28, 29]. Although telehealth applications are becoming increasingly popular in dentistry, controlled assessments of clinical outcomes, long-term use and economic analyses of teledentistry are still limited [30–32]. A comparison of the costs of teledentistry and its alternatives is of great importance to those making future decisions about implementing a new service. In this study, we propose a paradigm shift in the existing dental services through role substitution and taking advantage of user-friendly mobile technology and the widely available Internet to improve school children access to dental services.

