#### Visual dental examination

A standard dental screening (without radiography) will be performed by registered OHTs (operators) who are blinded to the group allocation of the school. Head-mounted lighting, disposable mirrors and probes will be used to conduct the visual dental screening. Findings from the visual dental assessment will be recorded on an oral health assessment form that follows the guidelines for oral health surveys developed by the WHO [35]. Following the completion of the baseline dental screening, parents of school children allocated to the control group will receive a copy of the screening results based on the visual inspection performed by onsite OHTs. Based on the severity and urgency of dental conditions, children with active caries will be referred to local dental providers for further investigations. Children who are screened caries-free or at low-risk, will not receive active treatment other than OHP leaflets.

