### Process evaluation

Regular auditing for OHTs will be conducted by an independent researcher to assess the intervention fidelity and determine whether the study protocol was followed as intended. Tele-assistants collecting dental images and OHTs participated in the charting of dental images will be surveyed to explore their acceptability of school dental screening based on dental photography.

To maximise retention of participants, all participants will receive a letter at the baseline on the importance of adhering to the intervention and on participation in the follow-up measurements as well as expected benefits including a free dental examination conducted within schools, and receiving screening report that includes preventive interventions to promote tooth brushing and healthy diet. To promote their active participation in the study, participants will receive Bright Smiles dental kits (consisting of toothbrush and toothpaste) at the end of the study.

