### Data analysis

The sensitivity and specificity values for the photographic caries assessment will be estimated and compared to the reference visual dental assessment at the baseline. Kappa statistic will be used to estimate the inter-rater reliability of the photographic dental assessments by two independent OHTs. 15% of dental images will be re-examined to test intra-rater reliability at least, 4 weeks after the initial review of images.

The baseline data will be used to generate descriptive statistics for the intervention and control groups (teledental versus usual care pathway). General linear regression models will be performed to compare the efficacy of the interventions on decay (mean DFT/dft) between intervention and control groups, adjusting for baseline data collected via a survey that includes tooth brushing (yes/no; frequency); dental visit patterns over the past year, child age, Indigenous status, Socio-Economic Indexes for Areas (SEIFA), private insurance status and educational level of parents. The measure of intervention efficacy will be the difference between the intervention and control groups in adjusted DFT/dft (caries incidence) per child. All analyses will be performed using SAS (version 9.4). In addition, a cost minimisation analysis will be undertaken to compare the costs associated with teledental versus the usual pathway of dental care over 9 months. This will include both the cost of the initial screening, and any subsequent interventions occurring over the 9 months. The analysis will be conducted from the perspective of the health system and, will not take into consideration the costs incurred by the families. All salaries used in the calculation will be based on Australian government rates and will include on-costs.

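### The hypothesis that photographs equal visual screening in accuracy and reliability cannot be tested by an analysis that uses visual screening as the reference and describes reliability checks for photographs only

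*Protocol article*

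**What the plan says.** In the Objectives section, the third objective is "To assess the diagnostic performance of dental screening on the basis of dental images relative to the reference visual dental inspection at the baseline". Its hypothesis follows directly: "The photographic dental assessment will be as accurate and reliable as the standard visual dental screening".

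The Data analysis section gives the accuracy analysis: "The sensitivity and specificity values for the photographic caries assessment will be estimated and compared to the reference visual dental assessment at the baseline". On reliability it says "Kappa statistic will be used to estimate the inter-rater reliability of the photographic dental assessments by two independent OHTs" and "15% of dental images will be re-examined to test intra-rater reliability at least, 4 weeks after the initial review of images".

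The subsection Visual dental examination sets out how the reference is obtained: "A standard dental screening (without radiography) will be performed by registered OHTs (operators) who are blinded to the group allocation of the school". Under Process evaluation there is an audit: "Regular auditing for OHTs will be conducted by an independent researcher to assess the intervention fidelity". The Background summarises the earlier validation work as having "offered a moderate diagnostic accuracy relative to visual dental screening".

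**The concern.** The objective and the hypothesis ask different questions. The objective asks how photographs perform against visual inspection. The hypothesis ranks the two methods as equals on accuracy and on reliability. To rank two methods on accuracy, both must be scored against something outside the pair. To rank them on reliability, both need a repeatability measure. The article describes neither.

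Two wrong conclusions become possible. Ordinary error in the visual examination could make an equally accurate photographic method look worse. Or a high kappa among image readers could be reported as reliability equal to visual screening, with no visual figure beside it. The Discussion uses image-based screening to argue for trained non-dental personnel on the front line, so the wording of this conclusion matters beyond the trial.

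**Working it through.** **1. What the study was sized for.** Inputs from Sample size calculation: 95% confidence (Z = 1.96), m = 0.1, expected proportion 0.90, prevalence 35%, dropout 20%.
- Children with caries: 1.96² / 0.1² × 0.90 × 0.10 = 34.57, rounded up to 35. This matches the plan.
- Total: 35 / 0.35 = 100, so 65 without caries. This matches.
- After dropout: 100 / 0.80 = 125 per group. This matches.

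The formula fixes the precision of one proportion, and m is the half-width of its interval. With 35 children with caries the half-width is 1.96 × √(0.09/35) = 0.099; with 87.5 (35% of 250) it is 0.063. That suits an estimate of agreement with visual screening. It is not a comparison of two methods.

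**2. Accuracy.** Against itself, the visual reference has sensitivity and specificity of 1.00. Photographs can equal that only by agreeing on every classification. An expected value of 0.90 is already below it.

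**3. Illustration of the consequence.** Assumptions not in the documents: both methods share the same true sensitivity Se and specificity Sp, and their errors are independent given true status. Prevalence p = 0.35 is the plan's.

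- Apparent sensitivity = [p·Se² + (1−p)(1−Sp)²] / [p·Se + (1−p)(1−Sp)]
- Apparent specificity = [p(1−Se)² + (1−p)Sp²] / [1 − p·Se − (1−p)(1−Sp)]

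Se/Sp = 0.80/0.95:
- sensitivity = (0.2240 + 0.0016) / 0.3125 = 0.722
- specificity = (0.0140 + 0.5866) / 0.6875 = 0.874

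Se/Sp = 0.90/0.98:
- sensitivity = (0.2835 + 0.0003) / 0.3280 = 0.865
- specificity = (0.0035 + 0.6243) / 0.6720 = 0.934

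**4. Range over error correlation.** Let r be the within-class correlation of the two methods' errors. Add r·Se(1−Se) to Se² and to (1−Se)², and r·Sp(1−Sp) to Sp² and to (1−Sp)².

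| True Se/Sp | r = 0 | r = 0.5 | r = 1 |
|---|---|---|---|
| 0.80/0.95 | 0.72/0.87 | 0.86/0.94 | 1.00/1.00 |
| 0.90/0.98 | 0.87/0.93 | 0.93/0.97 | 1.00/1.00 |

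True accuracy is constant along each row, yet apparent sensitivity runs from 0.72 or 0.87 up to 1.00. At r = 1 in the first row, agreement is perfect although both methods miss 20% of children with caries. Observed agreement therefore reflects accuracy and shared error together, and the analysis cannot separate them.

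**5. Reliability.** Both planned reliability measures concern images. The audit of oral health therapists concerns fidelity and adherence to the protocol. The 9-month visual check-up follows advice and possible treatment, so it records change in status, not repeatability. No visual kappa is described.

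**The case against.** The strongest reply is that this is one loose phrase in a secondary outcome. The objective, the sizing at 0.90 and the analysis fit one another, and the Background openly describes accuracy as relative to visual screening. This stands. A reader might infer that the diagnostic part of the design fails altogether. The documents do not support that, because performance relative to visual inspection can be estimated as planned.

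A reader might also infer that the reliability of visual examiners is never measured in this trial. That goes too far: an article condenses a fuller protocol, and examiner calibration or duplicate examinations could be described there. All that can be said is that none is described here. Such data would supply a comparator for reliability, but would leave the accuracy problem in place.

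The size of the gap is also open to challenge. Both methods look at the same teeth under WHO-based criteria, so positively correlated errors are plausible and independence may overstate the gap. At r = 0.5 the apparent sensitivity in the second scenario is 0.93, above the planned 0.90. Caries is charted per tooth, whereas 35% is a prevalence among participants, so the figures may not match the unit analysed. They are an illustration, not a forecast.

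Finally, a reader might take 0.90 − 0.10 = 0.80 as the plan's own pass mark. The text calls 0.1 an effect size, but in the formula it is the interval half-width, so the plan sets no such threshold. Nor would that mark protect an equal method: with 87 visually positive children (about 35% of 250), the lower limits in the two independent-error scenarios would be 0.722 − 1.96 × √(0.722 × 0.278/87) = 0.63 and 0.865 − 1.96 × √(0.865 × 0.135/87) = 0.79, both below 0.80.

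**Conclusion.** The point holds for the hypothesis, not for the objective. The accuracy part follows from the text alone: the comparator is also the reference, so equality could appear only as perfect agreement, and even that would not establish equal accuracy when errors are shared. The reliability part holds as far as this document goes, since repeat readings are described for photographs only.

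The shortfall that an equally accurate method might show has no fixed size. In the two assumed scenarios, apparent sensitivity is 0.72 and 0.87 with independent errors, about 0.86 and 0.93 at correlation 0.5, and 1.00 at full correlation. The defect should be corrected because it decides what may be concluded. It is a mismatch between a stated hypothesis and its analysis in a secondary outcome, and does not invalidate the planned estimates.

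**What to change.** Restate the third hypothesis and its conclusion as agreement of photographic with visual assessment. Report sensitivity and specificity against visual screening with 95% confidence intervals. Delete the wording that claims equal accuracy and reliability. Report inter-rater and intra-rater kappa as properties of photographic assessment only, with no claim of equality to visual reliability.

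If the sponsor wants a pass/fail criterion, it should justify a minimum acceptable agreement in advance, and should not present 0.80 as the plan's own threshold.

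The change rewords one hypothesis and its conclusion and needs no new data. The price is a more modest claim.

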## Methods

This community-based project is a parallel, two-armed, non-inferiority randomised controlled trial (RCT) that seeks to determine the efficacy and net economic benefits of using telehealth to facilitate dental care delivery within school settings and aid in generating data which will assist to leverage the planning and justification for a multicentre large RCT. The study will be conducted in accordance with the SPIRIT Statement for reporting a clinical trial protocol [33] (checklist provided as Additional file 1).

### Web-based and mobile applications

Software engineers from the CSIRO’s Australian e-Health Research Centre (AEHRC), developed a reliable electronic health record system ‘Remote-I’ based on store-and-forward technology. There are two components of the prototype of the existing teledentistry system, (1) an image acquisition mobile App ‘Teledental’ to facilitate entry of patient information and capturing dental images, and then transferring the data to a secure drive using Wi-Fi or 4G network (Fig. 1). Capturing and reviewing images and lighting functions will be integrated into a single mobile App installed on a smartphone; and (2) web-based platform application ‘Remote-I’ for storage, viewing and charting of dental photographs (Fig. 2). The Remote-I system has been used in tele-retinal screening for diabetic retinopathy [34] and it was recently modified so it can be employed for dental screening purposes [25]. More information about the Remote-I and image acquisition mobile App are described in a previous study [25]. For this study, four Samsung® S7 devices with mobile Internet plan will be used in dental photography.

**Fig. 1 Fig1:**
[figure not shown]
Teledental App used in dental photography

**Fig. 2 Fig2:**
[figure not shown]
Screenshot of the Remote-I system depicting dentogram and dental images

### Study setting

The study will take place in a school setting in Australia from 2018 to 2020. Participants will be recruited from schools in different geographical locations across WA.

### Participants’ recruitment

We will approach approximately 25 schools in WA, initially by email with a telephone follow-up, complying with good practice and research governance for undertaking studies within the education system. Parents of children aged 4–15 years, attending selected schools, will be invited to allow their children to take part in research using several advertising strategies including, schools’ newsletters, email lists and notice boards to help in achieving target sample. The inclusion criteria include children, aged 4–15 years, who are attending schools or college in WA in which the school principal has permitted for their school to be included in the trial will be included in the study, subject to their parents giving written consent. The exclusion criteria include children of the same age, in the same schools for whom parents have not given written permission for their children to take part. Once written permission is obtained from the schools, an information sheet and consent form will be mailed to parents of school children attending participating schools to invite them to participate. Besides, an information session will be scheduled for parents to provide more information about the project and respond to their enquiries.

### Allocation

To avoid spill-over effects within a school, we will conduct randomisation using the school as the unit of allocation because the intervention is implemented at the level of the school (Fig. 3). The schools will be randomly allocated in a 1:1 ratio to one of the teledental or control group. For allocation of the participants, a computer-generated list of random numbers will be used. To approximate equality of sample sizes in the study groups, we will use block randomisation with computer-generated randomly permuted blocks of 4 at each school. School-specific randomisation lists are concealed by an independent researcher, and kept in sequence and opened as participants are examined at the baseline and found eligible for enrolment. The research team and data analysts will be blinded to group allocation and will not be aware of the randomisation procedure. Study participants (and their parents/guardians) and OHTs providing the intervention and/or collecting data cannot be blinded to group allocation.

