### Sample size calculation

The sample size calculation is based on a two-sided 95% CI for a single proportion using the Z-test approximation, an effect size of 0.1 and an expected observed proportion of 0.90. The number of participants with caries that meet the power of 0.8 is estimated to be 35 [n ≥ (Z^2^/m^2^) p (1 - p)]. With the prevalence of caries at 35% (1.86 × 65), 65 participants without caries are needed. After considering a 20% drop out rate, the proportion that gives the largest sample size shows that at least 125 children per group will be needed. Three schools will be required in each group with a maximum of 45 children in each school.

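### The Allocation section names the school as the unit, then describes child-level lists in fixed blocks of 4; if those lists are really used, up to one third of assignments could be predicted

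*Protocol article*

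**What the plan says.** The Allocation section of the protocol article opens with the school as the unit: "we will conduct randomisation using the school as the unit of allocation because the intervention is implemented at the level of the school". It adds "The schools will be randomly allocated in a 1:1 ratio to one of the teledental or control group" and gives avoidance of spill-over within a school as the reason. The abstract, and the sample size section ("Three schools will be required in each group with a maximum of 45 children in each school"), describe the same design.

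The same paragraph then turns to children: "For allocation of the participants, a computer-generated list of random numbers will be used", and "we will use block randomisation with computer-generated randomly permuted blocks of 4 at each school". On concealment it says "School-specific randomisation lists are concealed by an independent researcher", and that the lists are "kept in sequence and opened as participants are examined at the baseline and found eligible for enrolment".

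On blinding, the Allocation section says that the research team and analysts are blinded and do not know the randomisation procedure, but that families are not blinded and "OHTs providing the intervention and/or collecting data cannot be blinded to group allocation". The section on the visual dental examination says instead that the OHTs who do the screening are blinded to the arm of the school.

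**The concern.** Lists within a school, balanced in blocks, put both arms into the same school. That is the mixing which allocation by school is meant to prevent. A reader therefore cannot tell which randomisation was carried out.

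If the child lists are real, three stated features combine badly: one small block size, sequential opening at the site, and data collectors described as unblinded. Concealing the list hides future entries, but not the past ones from which the rest of a block can be worked out.

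The baseline visual examination is the point at risk. It identifies urgent referrals, sets baseline DFT/dft, and defines which teeth were caries-free, so it anchors both primary outcomes. Enamel-level lesions count as carious, which leaves room for judgement. In a non-inferiority comparison, baseline scoring or examination order influenced by the expected arm could push the result in either direction.

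**Working it through.** **The plan's own figure.** The article gives no predictability figure, so its head count is the figure to reproduce first. The inputs, all from the sample size section, are a 95% CI (Z = 1.96), m = 0.1, p = 0.90, prevalence 35% and dropout 20%.

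- With caries: (1.96² / 0.1²) × 0.9 × 0.1 = 34.57, rounded up to 35.
- Without caries: 35 × 0.65 / 0.35 = 65. Total 100.
- With dropout: 100 / 0.8 = 125 per group, 250 in all.

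This matches the article. It serves below only as the number of children.

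**Reading A: the school is the unit.** Once a school is allocated, the arm of every child in it is fixed. No child-level block exists, and a predictable share of child assignments has no meaning. The block text is then simply in conflict with the design.

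**Reading B: children are allocated from school-specific lists.** Take blocks of 4 with two teledental (T) and two control (C) places. The six orders are equally likely. An assignment is certain once one arm has used both its places.

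| Order | Certain assignments |
|---|---|
| TTCC | 2 |
| CCTT | 2 |
| TCTC | 1 |
| TCCT | 1 |
| CTCT | 1 |
| CTTC | 1 |

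- Certain share: (2 × 2 + 4 × 1) / (6 × 4) = 8/24 = 33.3%.
- Over 250 children: 250 / 3 = about 83.
- In a school of 45 (11 full blocks and one child over): 11 × 4/3 = 14.7, and 14.7 / 45 = 32.6%.

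For the best guess, always name the arm with more places left and toss a coin when they are equal. The chance of being right at positions 1 to 4 is 1/2, 2/3, 2/3 and 1. At position 3 it is 1/3 × 1 + 2/3 × 1/2 = 2/3. The average is (1/2 + 2/3 + 2/3 + 1) / 4 = 17/24 = 70.8%, against 50% by chance.

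**Effect of a different scheme under reading B.** The certain share is 1/4 for fixed blocks of 6 and 1/5 for fixed blocks of 8. For blocks randomly mixed between 4 and 6, with the current size hidden from the observer, simulation with 45 children per school gave about 6%. That mix is an assumption for illustration, not something in the article.

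**What the upper bound requires.** The observer must know the block size and the balance within it, and must see every earlier assignment in that school in order. The article does not say who opens the lists or who sees the result.

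**The case against.** A reader might infer that one third of this trial's assignments were known in advance. The documents do not support that, for four reasons.

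- The abstract, the opening of the Allocation section, the visual examination section and the sample size section all point to the school as the unit. Under that reading the one third disappears.
- The screening OHTs are said in one place to be blinded, and the research team is said not to know the procedure. The article gives the block size while data are being collected, which weakens that safeguard but does not show that site staff knew it.
- All children are both examined and photographed. The arm decides only which results the parents receive, and these follow the baseline screening. Only the opening of the list could reveal the arm at the visit.
- Eligibility is age, attendance at a participating school, and parental consent. No clinical criterion lets an examiner turn a child away.

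These points stand. They make the figures conditional upper bounds, and they make examination order and scoring the plausible routes to bias, more than exclusion of children. They do not remove the contradiction over the unit, and the blinding safeguard is itself contradicted within the article.

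A reader might also carry the blocks of 4 over to the list of schools and infer that unequal numbers of schools per arm are likely. The article places the blocks within each school and fixes three schools per group, so that inference has no basis.

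Finally, a change to the lists may come too late. Analysis was to be complete in July 2020 and follow-up is at 9 months, which puts baseline at about October 2019 or earlier if that date held. This is fair, and is why part of the remedy lies in reporting.

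**Conclusion.** The concern holds in a conditional form. The Allocation section describes two incompatible schemes, and blocks of 4 serve the design well under neither. Under school allocation they have no function. Under child allocation they allow up to one third of assignments to be known with certainty, and up to 71% to be guessed correctly. Those figures assume 2:2 blocks and an on-site observer who knows the block size and sees all earlier assignments. The documents show neither that such an observer existed nor that any bias resulted, and its size cannot be estimated from them. The two statements on OHT blinding conflict and must be reconciled whichever unit applies. This should be corrected, with medium confidence in its practical effect.

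**What to change.** 1. State one unit of allocation.
2. If it is the school, delete the child lists and the blocks of 4, and state that the independent researcher allocates the participating schools in one draw constrained to equal numbers per arm (3:3). If schools are already allocated, describe how it was done.
3. If child lists are really used, replace the fixed block with randomly varying sizes not disclosed to site staff, and release each assignment singly, only after that child's baseline visual form is locked.
4. Reconcile the blinding statements in the Allocation and visual dental examination sections, saying which OHTs know the arm and from what point.
5. For any children already allocated by fixed blocks, report baseline DFT/dft for determined versus undetermined block positions, by arm so that opposite shifts do not cancel. This is a check for selection or scoring bias.

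The cost is protocol wording, a list regenerated by the same independent researcher if allocation is still open, and one extra table. No additional staff or participants are needed. The downside of varying block sizes is slightly unequal arm sizes within a school.

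### The Allocation section describes both school-level and within-school child-level randomisation, and it contradicts the examination section on examiner blinding; the two allocation readings need different analyses

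*Protocol article*

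**What the plan says.** **Unit of allocation.** The Allocation section of the protocol article first says "we will conduct randomisation using the school as the unit of allocation because the intervention is implemented at the level of the school", and gives avoidance of spill-over within a school as the reason. It continues: "The schools will be randomly allocated in a 1:1 ratio to one of the teledental or control group". The Abstract and the Sample size calculation section agree, with about three schools per arm.

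The same paragraph then turns to children: "For allocation of the participants, a computer-generated list of random numbers will be used". To balance the group sizes, "we will use block randomisation with computer-generated randomly permuted blocks of 4 at each school". The lists are specific to each school, are concealed by an independent researcher, and are "kept in sequence and opened as participants are examined at the baseline and found eligible for enrolment".

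**Blinding.** The Allocation section ends by saying that "OHTs providing the intervention and/or collecting data cannot be blinded to group allocation". The Visual dental examination section says the screening is done by "registered OHTs (operators) who are blinded to the group allocation of the school".

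**Analysis.** The Data analysis section compares mean DFT/dft between arms with general linear regression, adjusting for survey covariates. It states no term for school.

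**The concern.** A list that belongs to one school and is opened as each child is found eligible has a function only if children within that school can receive different assignments. Both arms would then be present in every school, which is what school allocation was meant to prevent. If the school really is the unit, every entry on its list would be the same, and blocks of 4 would have no role.

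Two things are at stake. First, the unit of randomisation fixes the valid variance. Under school allocation there are six independent units, and a child-level model that ignores school gives confidence intervals that are too narrow. Under child allocation within schools the variance problem goes away, but spill-over could draw the arms together. The trial is described as non-inferiority, and both faults make it easier to conclude that the arms do not differ by much.

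Second, the primary outcome counts enamel-level caries, which calls for examiner judgement. Whether the examiner knew the arm bears directly on how far the result can be trusted, and the two statements on this cannot both be true of the same therapists.

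**Working it through.** **1. The plan's own figure.** Inputs from the Sample size calculation section: two-sided 95% interval (Z = 1.96), half-width m = 0.1, proportion p = 0.90, caries prevalence 35%, dropout 20%.
- With caries: Z²p(1 − p)/m² = 1.96² × 0.90 × 0.10 / 0.1² = 34.57, rounded up to 35.
- Total at 35% prevalence: 35/0.35 = 100, so 65 without caries.
- After dropout: 100/(1 − 0.20) = 125 per group.

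The stated 125 is reproduced. Nothing in this calculation depends on the unit of allocation, so it does not show which reading was intended.

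**2. The two procedures side by side.**

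| Feature | School as unit | Child as unit within school |
|---|---|---|
| Where stated | Abstract; opening of Allocation; Visual dental examination; Sample size calculation | Later sentences of Allocation only |
| What is randomised | About six schools, 1:1 | Children, blocks of 4 in each school |
| When the assignment is opened | Not described | As each child is found eligible |
| Arms present in a school | One | Both |
| Spill-over protection | Yes | No |
| Independent units | 6 schools | About 250 children |
| Role of school in the analysis | Cluster | Stratum |

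No single procedure satisfies both columns.

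**3. Size under school allocation.** Completers per school: 125 × 0.80 / 3 = 33.3. The article gives no ICC, so 0.01 to 0.05 is an assumption. Design effect (DE) = 1 + (33.3 − 1) × ICC.

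| Assumed ICC | DE | Effective size of 100 completers per arm | Interval should be wider by √DE | Type I error of a nominal 5% two-sided test ignoring school |
|---|---|---|---|---|
| 0.01 | 1.32 | 75.6 | 1.15 | 8.8% |
| 0.02 | 1.65 | 60.7 | 1.28 | 12.7% |
| 0.05 | 2.62 | 38.2 | 1.62 | 22.6% |

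The last column is 2 × [1 − Φ(1.96/√DE)]. It is a large-sample figure and makes no allowance for there being only six clusters. Using the enrolled number per school instead (125/3 = 41.7) gives a DE of 1.41 at ICC 0.01 and 3.03 at ICC 0.05.

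These design effects compare school allocation with simple random sampling of children. Against randomisation within schools, where between-school variance drops out, the variance ratio is DE/(1 − ICC): 1.32/0.99 = 1.34 at ICC 0.01 and 2.62/0.95 = 2.75 at ICC 0.05.

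**4. Six clusters.** A school-level comparison has 6 − 2 = 4 degrees of freedom. A 3:3 split can be made in C(6,3) = 20 ways, so the smallest two-sided permutation p-value is 2/20 = 0.10.

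**5. Blinding.** The Abstract has all children examined and then photographed at baseline, so on-site procedures do not by themselves reveal the arm. At 9 months, the Follow up section has the check-up also establish what treatment was received and whether parents followed the advice. The Allocation section says families are not blinded. The Follow up section does not say whether the 9-month examiner is.

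**The case against.** The strongest reply is that the intended design is clear. School allocation is stated in the Abstract, twice in Allocation with a reason, and implied in the examination and sample size sections. The child-level text is one run of sentences. This stands as far as it goes: a reader might infer that the design is wholly undefined, and the documents do not support that. But the child-level sentences are the only description of how lists are made, concealed and opened. They are what trial staff would follow, and they give a different design.

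It may also be said that an analysis plan will settle the model. It can supply detail, but it cannot decide which of two stated allocation procedures was carried out.

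On blinding, the examination sentence sits under the baseline procedures, so the Allocation sentence could concern other therapists or the later visit. That is possible, but the Allocation sentence has no such limit, and the baseline examiners do collect data.

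Three stronger inferences are tempting and should not be drawn:
- That blocks of 4 were applied to the six schools and so threaten the 3:3 split. The blocks are within each school and the lists are opened per participant. The Abstract also says only approximately three schools per arm.
- That opening a school's assignment at its first child invites selective enrolment. Entry depends on age, school and written parental consent, and no stated criterion turns on examiner judgement. What remains is the examiner's awareness of the arm.
- That the 9-month outcome will be biased by unblinded examiners. The documents do not say who examines at 9 months or what they know, so the most that can be said is that it could be.

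**Conclusion.** Both contradictions are in the current text and nothing elsewhere in the article resolves them. They are conflicting statements, not detail left to another document. The allocation conflict must be settled because it decides the analysis. On the predominant school-level reading, the stated linear model understates the variance by a factor of about 1.3 to 2.6, if it is fitted without allowance for school. That range assumes an ICC of 0.01 to 0.05, equal school sizes, three schools per arm and the planned 20% dropout. On the child-level reading there is no such variance inflation, and omitting school costs only a little efficiency, but the claim of protection from spill-over fails. The blinding conflict cannot be given a size from the documents. It matters because the primary outcome includes a judgement on early lesions.

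**What to change.** The Study status section says data are being collected, so the first step is to report what was done.

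1. **State the procedure actually used**, school or child within school.
2. **If schools were allocated:** delete the sentences on participant-level blocks and lists, and describe one concealed list of schools. In the Data analysis section, account for school as the cluster with a method suited to six clusters, such as a school-level comparison on 4 degrees of freedom or a mixed model with a small-sample correction. A permutation test over 20 allocations cannot reach two-sided 5%.
3. **If children were randomised within schools:** withdraw the school-allocation and spill-over claims throughout, include school as a stratum, and discuss contamination.
4. **Where schools are the unit and a school's baseline is still to come:** release its assignment only after its children have been examined. This cannot be applied to schools already done.
5. **Blinding:** reconcile the Allocation and Visual dental examination sections by stating, separately for baseline and 9 months, whether the examining therapist knew the arm. Where feasible at 9 months, record caries before asking about treatment or adherence. Otherwise report unblinded assessment as a limitation. A blanket claim of blinding should not be added unless it is true of the later visit.

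The cost is protocol wording, a change of model and, where still possible, the order of two steps at a visit. No extra staff are needed. Under school allocation the honest interval will be wider, and redrafting cannot recover that precision.
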